### Assessments and endpoints

2.5

The schedule of study assessments is detailed in Table 3 below. The following assessments are conducted at baseline and week 6 of radiotherapy, then at 4 weeks, 3 months and 6 months after radiotherapy completion: MD Anderson Dysphagia Inventory score (MDADI) and quality of life questionnaires (EORTC QLQ-C30 and H&N43). Adverse events will be assessed, using CTCAE v5.0 [48], at baseline and weekly during radiotherapy until 4 weeks post completion, then at 3 and 6 months post radiotherapy. An optional sub-study will collect blood and saliva samples at baseline, weekly during radiotherapy and at week 4, then 3 and 6 months post radiotherapy. A further optional procedure for participants is to undergo a research biopsy from the primary tumour after ten fractions of radiotherapy (after MRI_2).1.CTCAE v5.0 will be used to grade acute toxicity, RTOG Radiation Morbidity Scoring Criteria will be used to grade late toxicity, at 3 & 6 months post completion of RT2.Quality of Life questionnaires include EORTC QLQ-C30 & H&N43

**Table 3 t0015:** –Schedule of assessments.

Study assessment	Baseline	RT Week 1	RT Week 2	RT Week 3	RT Week 4	RT Week 5	RT Week 6	Post-RT Week 1	Post RT week 2	Post RT week 3	Post RT week 4	Post RT 3 monts	Post RT 6 months
Performance status ECOG	X						X				X	X	X
Swallowing assessment (MDADI)	X						X				X	X	X
Toxicity review^1^	X	X	X	X	X	X	X	X	X	X	X	X	X
QoL Questionaires^2^	X						X				X	X	X
Translational blood & saliva sample	X	X	X	X	X	X	X				X	X	X
Research biopsy				X									

Loco-regional control rates at 12 and 24 months, as well as overall survival will also be collected from record review. Safety reporting will be carried out by the Pharmacovigilance Department of the Glasgow Oncology Clinical Trials Unit.

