**Secondary Endpoints:**

Proportion of Grade 3+ acute (up to 3 months) and early late (3–6 months) toxicity rates, comparing dose-escalated and standard radiotherapy cohorts.

Patient reported quality of life scores, comparing dose-escalated and standard radiotherapy cohorts.

Loco-regional control rates at 12 and 24 months, overall survival, and cancer specific survival; comparing dose-escalated and standard radiotherapy cohorts.

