### Statistics

2.6

A sample size of 20 patients will be targeted. Using a one-sided significance level of 0.05 and 80% power, the true success rate would need to be approximately 0.76, to demonstrate a success rate of greater than 50%. For the primary endpoint of feasibility, the proportion of patients able to complete DW-MRI guided response adapted radiotherapy will be reported with an exact 95% confidence interval. For the secondary safety analysis, the proportion of dose escalated patients experiencing grade III or IV RT-related toxicities will be compared with standard treatment patients using an odds-ratio with an exact 95% confidence interval. The time of onset and duration of severe toxicities, as well as the number of patients missing one or more treatment days, will also be reported. The number of patients achieving loco-regional control at 6-months follow-up will be reported, along with an odds ratio for the comparison of groups and an exact 95% confidence interval. Overall survival and cancer-specific survival will also be summarised at 6-months follow-up, presented with Kaplan-Meier plots and log -rank tests.

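### Section 2.6 analyses loco-regional control only at 6 months, which is not a listed endpoint; the secondary endpoint, control at 12 and 24 months, has no stated analysis in the article

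*Protocol article*

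**What the plan says.** Three statements in the protocol article bear on this point.

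- **Endpoint definition** (section 2.5, Secondary Endpoints): "Loco-regional control rates at 12 and 24 months, overall survival, and cancer specific survival; comparing dose-escalated and standard radiotherapy cohorts". Loco-regional control has two time points; the survival endpoints have none.
- **Data collection** (section 2.5, Assessments and endpoints): "Loco-regional control rates at 12 and 24 months, as well as overall survival will also be collected from record review". The scheduled visits in Table 3 end 6 months after radiotherapy, so the later outcomes depend on this record review.
- **Analysis** (section 2.6, Statistics): "The number of patients achieving loco-regional control at 6-months follow-up will be reported". The two cohorts are to be compared at that same time point by an odds ratio, for which an exact interval is planned. For survival: "Overall survival and cancer-specific survival will also be summarised at 6-months follow-up, presented with Kaplan-Meier plots", with log-rank tests.

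Neither the primary nor the exploratory endpoint list mentions loco-regional control, and the secondary list gives it only at 12 and 24 months.

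**The concern.** Section 2.6 does more than leave a detail to a later document. It fixes a time point, an effect measure and an interval for loco-regional control, and the time point is not the one that section 2.5 defines. Someone following 2.6 literally would collect the 12- and 24-month rates and have no instruction to analyse them, while reporting a 6-month comparison that no endpoint list contains.

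Two things are at stake. First, with two unreconciled sets of time points, the result put forward could be chosen after the data are seen. Second, the introduction says failure in this disease is mainly loco-regional and uses that to justify dose escalation. Loco-regional control is therefore the disease outcome closest to the trial's rationale, and the earliest time point is the one with the fewest failures to compare.

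**Working it through.** **1. The plan's own figure.** The article gives no sample size, power or expected rate for loco-regional control or survival. Its only such figure belongs to the primary endpoint: "A sample size of 20 patients will be targeted", then "Using a one-sided significance level of 0.05 and 80% power", for a true completion rate of about 0.76 against 0.50. The one-sided normal approximation gives

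n = (1.645·√(0.5·0.5) + 0.842·√(0.76·0.24))² / (0.76 − 0.50)² ≈ 20.7,

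and with n = 20 the detectable rate is 0.764. The figure reproduces and plays no part in this point.

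**2. The sections side by side.**

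| Outcome | Endpoint list (2.5) | Collected by record review (2.5) | Analysed (2.6) |
|---|---|---|---|
| Loco-regional control | 12 and 24 months | 12 and 24 months | 6 months |
| Overall survival | no time point | no time point | 6 months |
| Cancer-specific survival | no time point | not named | 6 months |

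The first row is a contradiction. The other two are not: there is no stated time point for the 6-month wording to conflict with.

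**3. How few failures 6 months would give (illustration).** The article gives no loco-regional control rate, so I assume 24-month control C between 50% and 80% and a constant hazard. Expected failures in 20 patients by month t are 20·(1 − C^(t/24)).

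| Assumed 24-month control | By 6 months | By 12 months | By 24 months |
|---|---|---|---|
| 50% | 3.2 | 5.9 | 10.0 |
| 60% | 2.4 | 4.5 | 8.0 |
| 70% | 1.7 | 3.3 | 6.0 |
| 80% | 1.1 | 2.1 | 4.0 |

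By 6 months, 27% to 32% of the failures expected by 24 months would have occurred.

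**4. What a 6-month comparison could show.** Assume an even 10/10 split between cohorts. If all failures fell in one cohort, the two-sided Fisher p-value would be 2·C(10,k)/C(20,k), where C(a,b) is the number of combinations: 0.47 for k = 2, 0.21 for k = 3 and 0.087 for k = 4. Even the most extreme allocation of the expected failures is close to uninformative. An uneven split would change these values.

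**5. Survival (illustration).** The lowest 3-year overall survival in the introduction is 46.2%. With a constant hazard, λ = −ln(0.462)/36 = 0.02145 per month. Survival at 6, 12 and 24 months is then 0.879, 0.773 and 0.598, so expected deaths in 20 patients are 2.4, 4.5 and 8.0. Better survival means fewer. As an outer bound, the 93% 3-year survival quoted for favourable HPV-positive disease (not this trial's population) gives λ = −ln(0.93)/36 = 0.00202 and about 0.2, 0.5 and 0.9 deaths.

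**The case against.** The best defence is that the two sections fit together if read generously. The last scheduled visit is 6 months after radiotherapy, so 2.6 may describe a main report at that point, with the 12- and 24-month rates to follow from record review. Nothing in 2.6 says that the 6-month figure replaces the later ones, and an analysis plan that is not shown may contain the later analysis. This limits the claim: the absence of an analysis is established for this article only. It does not remove the mismatch. An analysis plan using 12 and 24 months would depart from 2.6, and one using 6 months would depart from the endpoint list in 2.5.

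Four stronger readings are tempting, and the document does not support them.

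- **That survival is contradicted too.** The endpoint list gives survival no time point.
- **That survival is censored at 6 months.** The wording could equally mean an analysis run once patients have reached that visit, with earlier recruits contributing longer follow-up. It is ambiguous and does not state truncation.
- **That the survival analysis discards about 70% of the deaths that will be on record** (2.4 of 8.0 used). This assumes that survival is followed to 24 months, whereas section 2.5 attaches 12 and 24 months to loco-regional control only.
- **That a competing-risks analysis is required.** It is a reasonable preference, but a time-point mismatch can be resolved without it, and it needs dates of failure, which the article does not say are collected.

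It is also fair to say that this is a 20-patient feasibility study whose hypothesis, sample size and 50% benchmark all concern completion of the workflow. The cohorts are formed by tumour response, so the comparison is non-randomised and confounded by prognosis at any time point. That limits what any of these analyses can show, but it does not justify analysing a time point other than the one named.

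**Conclusion.** The point holds for loco-regional control. As written, the secondary endpoint at 12 and 24 months has no analysis in the article, and the analysis that is stated, at 6 months, matches no listed endpoint. This rests on the text alone and needs no assumption.

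The consequence is that the reported time point is open to choice and that the 6-month comparison would rest on roughly 1 to 3 failures in 20 patients. That size depends on the assumed 50% to 80% control at 24 months and a constant hazard. The death counts of 2.4, 4.5 and 8.0 are illustrative only: they use the lowest survival figure in the article for a cohort that also includes HPV-positive patients with a smoking history. For survival, the article needs a clarification rather than a correction. The primary endpoint and its sample size are not touched.

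**What to change.** In section 2.6:

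1. State that loco-regional control is reported and compared between cohorts at 12 and 24 months, using the odds ratio with exact 95% confidence interval already planned.
2. Label any 6-month loco-regional control figure as an early descriptive summary.
3. State that the Kaplan-Meier and log-rank analyses of overall and cancer-specific survival use all available follow-up rather than stopping at 6 months.

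Make the change before outcome data by cohort are examined, so that the time point is fixed in advance.

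For loco-regional control this is a change of wording only, since section 2.5 already provides for collecting the 12- and 24-month rates. For survival, check that the record review captures dates of death and, for cancer-specific survival, cause of death over the same period; the article does not say. The downside is that the final secondary report comes later, after the 24-month data are in. The feasibility result can still be reported on its own schedule.

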MRI is the preferred imaging modality to accurately define the extent of OPSCC [21], [29]. Diffusion weighted MRI (DW-MRI) demonstrates the Brownian motion of water protons, also known as molecular diffusion. This can be quantified by the application of the apparent diffusion coefficient (ADC) which takes the microscopic motions of capillary perfusion and molecular diffusion into consideration, detailing the microstructure of the tissue of interest [30]. Previous studies have shown that ADC values can be applied to predict and monitor response to treatment [31], [32]. Solid masses hinder diffusion and have low ADC values. Several studies in HNSCC have shown that increases in ADC during treatment were significantly larger in tumours achieving a complete response [33], [34], [35], [36]. This specifically has been evaluated in poor prognosis OPSCC; an ADC assessment at baseline then fraction 10 of radiotherapy was found to appropriately categorise responding disease versus non-responding [37]. Primary disease with an increase in ADC of >17.8% was found to have a positive predictive value of 92.1% and a negative predictive value of 21.2% of long term disease control. This study mirrors findings from Wong et al.'s study, where a threshold ADC value of >17% and a nodal ADC of >27% was found to have positive predictive values of over 90% [38]. These studies suggest that serial DW-MRI may be used as an imaging biomarker to identify the sub-group of patients with poor prognosis OPSCC predicted to be failed by standard radiotherapy, and therefore may benefit from treatment intensification.

Adaptive radiotherapy is the process of adjusting the radiation plan during the course of treatment. This can be carried out with regards to anatomical changes, or response to treatment. Anatomical adaptive therapy accounts for the structural changes that can occur during treatment such as tumour reduction, weight loss or patient movement [39] and is commonplace during a radical treatment course. However, the concept of adaptive radiotherapy based on response assessment during treatment is not yet incorporated into clinical practice, but would allow individualisation of treatment.

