### DW-MRI scans

2.3

Baseline MRIs are obtained immediately prior to fraction one (MRI_1) and after ten fractions of radiotherapy (MRI_2). Sequences include 3D T2, DW (b numbers 0, 50, 100, 500, and 1000: all are used to calculate the ADC map), t1 FS Post Contrast and t2 dixon. GTVp and GTVn are outlined on each ADC map using anatomical and functional sequences to inform delineation. ADC is measured for each target volume and the % change in ADC is calculated between MRI_1 and MRI_2. Tumours deemed to be responding inadequately to radiotherapy (‘non-responders’) are those with an increase in GTVp ADC <18%, or GTVn ADC <27%, the remainder categorised as ‘responders’. ADC measurements and the categorisation of responders versus non-responders are overseen by the trial safety committee, which includes the principal investigator, project manager, study statistician, trial co-ordinator, trial monitor and sponsor's representative.

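### Escalated and standard cohorts are defined by tumour response, so the planned odds ratio for control and the log-rank tests cannot estimate an effect of dose escalation

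*Protocol article*

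**What the plan says.** Section 2.3 (DW-MRI scans) classifies tumours by the percentage change in ADC between the two scans. Inadequately responding tumours "are those with an increase in GTVp ADC <18%, or GTVn ADC <27%, the remainder categorised as ‘responders". Section 2.4 makes the choice of Phase II plan depend on that assessment: non-responders get the escalated plan and responders continue the standard one. There is no randomisation.

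The secondary endpoints in section 2.5 list loco-regional control at 12 and 24 months, overall survival and cancer-specific survival, each to be compared between the escalated and standard cohorts. Section 2.6 supplies the analyses. Control at 6 months is reported "along with an odds ratio for the comparison of groups and an exact 95% confidence interval". Overall and cancer-specific survival are "presented with Kaplan-Meier plots and log -rank tests". Neither section warns that the cohorts differ in prognosis by construction.

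The Introduction gives the reason for using the marker. A rise in primary-tumour ADC above 17.8% had a "positive predictive value of 92.1% and a negative predictive value of 21.2% of long term disease control", and serial DW-MRI is put forward as a way to "identify the sub-group of patients with poor prognosis OPSCC predicted to be failed by standard radiotherapy".

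**The concern.** The comparison is labelled by dose, but the groups are formed by response. Every escalated patient is a non-responder and every standard-dose patient is a responder. With no overlap between dose and marker, no covariate adjustment can separate them. The marker was selected because it predicts outcome, so the bias has a known direction: on the protocol's own rationale, the escalated cohort starts with the worse prognosis.

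What is at stake is how the secondary results are read. An odds ratio below 1, or a log-rank test favouring standard dose, could be taken as evidence against escalation when it reflects only the selection rule. A ratio near 1 could be taken as no effect when escalation had in fact closed the gap.

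**Working it through.** **The plan's own figure.** The only sample-size statement belongs to the feasibility endpoint: "A sample size of 20 patients will be targeted", and "Using a one-sided significance level of 0.05 and 80% power" a true rate of about 0.76 is needed against 50%. With the normal approximation and null variance, power = Φ[(√20·(p − 0.5) − 1.645·0.5)/√(p(1 − p))]. Setting this to 0.80 gives p = 0.764, which reproduces the stated figure. No size or power is given for the control or survival comparison.

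**Inputs for the illustration**, from the Introduction. The positive predictive value is read as the probability of control above the threshold, and the negative predictive value as the probability of failure below it.
- Responders: control 0.921, failure 0.079.
- Non-responders without escalation: failure 0.212, control 1 − 0.212 = 0.788.

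**Expected odds ratio for control, escalated versus standard.** The responder odds are 0.921/0.079 = 11.658. If escalation averts a share s of non-responder failures, their failure rate is 0.212·(1 − s).

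| Share averted | Non-responder control | Odds | Odds ratio v responders |
|---|---|---|---|
| 0 (no effect) | 0.788 | 0.788/0.212 = 3.717 | 0.32 |
| 50% | 0.894 | 0.894/0.106 = 8.434 | 0.72 |
| 63% (parity) | 0.921 | 11.658 | 1.00 |
| 75% | 0.947 | 0.947/0.053 = 17.868 | 1.53 |
| 90% | 0.9788 | 0.9788/0.0212 = 46.170 | 3.96 |

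The parity share is (0.212 − 0.079)/0.212 = 0.627. At parity the true effect of escalation among non-responders is an odds ratio of 11.658/3.717 = 3.14, yet the planned comparison shows 1.00.

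**Behaviour in 20 patients with no dose effect.** The article does not state the share of non-responders, so escalated:standard splits of 6:14, 8:12, 10:10, 12:8 and 14:6 were taken as an assumed range.
- Expected failures in total: 6·0.212 + 14·0.079 = 2.4 at 6:14; 2.12 + 0.79 = 2.9 at 10:10; 14·0.212 + 6·0.079 = 3.4 at 14:6.
- By exact binomial enumeration, the escalated cohort shows the lower control rate with probability 0.70 to 0.79.
- Fisher's test reaches p ≤ 0.05 in 0.3% to 9% of trials.
- An illustrative result of 8/10 versus 9/10 gives a conditional odds ratio of 0.46, exact 95% CI 0.007 to 10.5.

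The statistic is thus biased in a known direction and very imprecise.

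**Survival.** The documents give no survival by ADC response, so the log-rank point is one of direction only: the same confounding applies, but its size cannot be derived.

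**The case against.** The strongest reply is that this is a 20-patient feasibility study and these endpoints are secondary. The article attaches no success criterion to them and does not say that the comparison will be read as the effect of escalation. Its only futility threshold, under Primary Endpoint in section 2.5, is the 50% completion target. The exact interval would also show openly how little information there is. All of this stands and limits the severity. It does not make the comparison interpretable, because a wide interval signals imprecision and not bias.

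It is also fair that the predictive values are borrowed. They concern long-term control and a 17.8% primary-tumour threshold. The trial classifies on the primary or the nodes, and section 2.6 analyses control at 6 months. The article does not give the dose or any concurrent chemotherapy in the study that supplied them. So 0.32 is an illustration and not a forecast of the trial's result.

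Three stronger readings are tempting but unsupported:
- **That escalation could look at best neutral even if it fully works.** Nothing in the Introduction caps the effect at parity. Averting more than about 63% of non-responder failures gives an odds ratio above 1.
- **That these comparisons could decide whether the strategy moves to a randomised study.** The Discussion mentions later randomised studies, but no progression rule rests on control or survival.
- **That the plan intends to read a high control rate among escalated patients as benefit.** The Introduction's description of the sub-group sits awkwardly with 78.8% control below the threshold, but no such reading is planned.

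**Conclusion.** The point holds for the secondary endpoints of control and survival. Because ADC response alone fixes the cohort, the between-cohort odds ratio and log-rank tests cannot estimate an effect of escalation, and the article states no caveat. This conclusion rests on the design and needs no numerical assumption.

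The size is illustrative: an odds ratio of about 0.32 with no dose effect and 1.0 at parity. It assumes that the long-term, primary-tumour predictive values carry over to this population, time point and classification rule, which the documents do not show. The primary endpoint, the sample size and the 50% threshold are untouched. It should be corrected, but it is not a defect that undermines the trial.

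**What to change.** - In section 2.6, delete the between-cohort odds ratio for loco-regional control and the log-rank tests.
- Report control within each cohort with an exact 95% confidence interval, and survival within each cohort by Kaplan-Meier.
- In the secondary endpoints of section 2.5, reword the control and survival item as descriptive by cohort.
- Add one sentence stating that the cohorts differ in prognosis by design, so no dose effect is inferred from differences between them.

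The predictive values should not become a formal benchmark for the escalated cohort. They come from another study with a different rule and time point, and at about ten patients an observed 8/10 has an exact 95% interval of 44% to 97%.

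The cost is a wording change and the loss of a nominal p-value that could not be interpreted. No extra patients or data are needed.

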## Introduction and background

1

Head and neck cancer is the 9th most common cancer in the UK, with 12,800 new cases annually, and numbers expected to rise to 16,300 by 2040 [1]. Increasing numbers of patients with oropharyngeal squamous cell cancer (OPSCC) is not only due to the well documented growing incidence of the Human Papillomavirus (HPV), but also due to an increase in HPV-negative cancers [2]. Between 2010 and 2020, the rate of OPSCC increased by a factor of 2·1, and this is projected to more than double between 2020 and 2039 [3]. Survival is known to be favourable with HPV-positive disease, with a 3 year survival of 93%, leading to the consideration of possible treatment de-escalation [4], [5]. However, patients with HPV-negative cancers, and those with a substantial smoking history regardless of tumour HPV status, have poorer survival outcomes, with a 3 year overall survival as low as 46.2% [4], [6]. While HPV-negative and HPV-positive disease are different entities, prognosis is affected by smoking history in addition to tumour HPV status. Poorer outcomes, compared to the HPV-positive non-smoking population, is seen in both groups, with a common unmet need to improve disease control and survival. With a plethora of negative studies examining uniform de-intensification for HPV-positive OPSCC there is now acceptance that a more personalised approach to de-escalation of treatment is required [7], [8], [9], [10]. For example, promising results have been demonstrated in the Phase II setting using 18F- fluoromisonidazole Positron Emission Tomography (F-MISO PET) to guide hypoxia-directed dose de-escalated radiation [11]. Attempts to uniformly intensify treatment in the poorer prognosis populations have similarly been unsuccessful to date, both in the oropharyngeal [12] and non-oropharyngeal sub-sites [13]. An imaging biomarker to guide intensification of treatment for the poorer prognosis population remains an urgent unmet need.

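### Plain log-rank tests for 6-month survival in 20 patients would rest on about two or three deaths, too few for the usual chi-square p-value (minor)

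*Protocol article*

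**What the plan says.** Section 2.6 (Statistics) states: "A sample size of 20 patients will be targeted". The completion proportion is to carry an exact interval. Grade III or IV toxicity is compared between cohorts "using an odds-ratio with an exact 95% confidence interval", and loco-regional control is reported "along with an odds ratio for the comparison of groups and an exact 95% confidence interval". The next sentence turns to survival: "Overall survival and cancer-specific survival will also be summarised at 6-months follow-up", "presented with Kaplan-Meier plots and log -rank tests". No exact or permutation version, significance level or expected number of deaths is given for these tests.

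Section 2.5 lists overall and cancer-specific survival among the secondary endpoints, each comparing the dose-escalated with the standard cohort. Section 2.3 assigns patients to those cohorts by change in ADC, so the split is an outcome of the study and not a design choice. The only survival figure for the poor-prognosis population is in section 1: "3 year overall survival as low as 46.2"%.

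**The concern.** The ordinary log-rank p-value refers a statistic to a chi-square distribution, which is a good approximation only when there are enough events. Of the cohort comparisons described in section 2.6, survival at 6 months is likely to have very few events, and it is the only one not given an exact method. If the smaller cohort is very small, one or two deaths that are compatible with chance could be printed with a p-value below 0.05. In a dose-escalation study such a figure could be read as a signal of harm or benefit and carried into the planning of the larger trials that the Discussion foresees.

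This point concerns only how the p-value is calibrated. That the cohorts are defined by tumour response, so that no p-value isolates an effect of dose, is a separate matter.

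**Working it through.** **The plan's own figure.** The plan gives no event count or power for survival. Its one calculated figure belongs to the primary endpoint: "Using a one-sided significance level of 0.05 and 80% power, the true success rate would need to be approximately 0.76". The null value there is 50% completion. With the normal approximation, p₁ = 0.5 + 1.645 × 0.5/√20 + 0.842 × √(p₁(1 − p₁)/20) gives p₁ = 0.764, so it reproduces. The 20 patients were therefore sized for completion, not for survival.

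**Expected deaths (assumption: constant hazard).** Hazard = −ln(0.462)/36 = 0.0215 per month. Risk of death by 6 months = 1 − exp(−6 × 0.02145) = 0.121. Expected deaths = 20 × 0.121 = 2.4. With deaths distributed as Binomial(20, 0.121), the chance of none is 7.6%, of at most two 56%, and of at most three 78%. If 3-year survival were 60% to 70%, the expected number would be 1.6 to 1.2.

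**Single outcomes.** No censoring before 6 months and no ties are assumed. At each death, with n₁ of n still at risk in the smaller cohort, E = n₁/n and V = (n₁/n)(1 − n₁/n). Chi-square = (ΣO − ΣE)²/ΣV. The exact p is the probability, when deaths fall at random among those at risk, of an ordering at least as extreme.

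- One death, in the cohort of 4 (4:16): E = 0.20, V = 0.16, chi-square = 0.80²/0.16 = 4.00, p = 0.046. Exact p = 4/20 = 0.20.
- Two deaths, both in the cohort of 6 (6:14): ΣE = 6/20 + 5/19 = 0.563, ΣV = 0.210 + 0.194 = 0.404, chi-square = 1.437²/0.404 = 5.11, p = 0.024. Exact p = (6/20)(5/19) = 0.079.
- Four deaths, all in one cohort (10:10): ΣE = 1.830, ΣV = 0.988, chi-square = 2.170²/0.988 = 4.76, p = 0.029. Exact p = 2 × (10·9·8·7)/(20·19·18·17) = 0.087.

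Other cases with every death in the smaller cohort:

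| Split | Deaths | Log-rank p | Exact p |
|---|---|---|---|
| 3:17 | 1 | 0.017 | 0.15 |
| 5:15 | 1 | 0.083 | 0.25 |
| 4:16 | 2 | 0.002 | 0.032 |
| 5:15 | 2 | 0.010 | 0.053 |
| 7:13 | 2 | 0.045 | 0.11 |
| 8:12 | 2 | 0.073 | 0.15 |
| 8:12 | 3 | 0.023 | 0.049 |
| 9:11 | 3 | 0.042 | 0.074 |
| 10:10 | 3 | 0.067 | 0.21 |

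So one death is enough for p < 0.05 only if the smaller cohort has at most 4 patients, and two only if it has at most 7. The error can also run the other way: at 5:15, a death in the smaller cohort followed by one in the larger gives 0.364 against an exact 0.25.

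**True size of a nominal two-sided 5% test.** All orderings of deaths were enumerated under the null, and the result was averaged over Binomial(20, 0.121):

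| Split | 2:18 | 3:17 | 4:16 | 5:15 | 6:14 | 7:13 | 8:12 | 9:11 | 10:10 |
|---|---|---|---|---|---|---|---|---|---|
| Size | 0.061 | 0.062 | 0.079 | 0.025 | 0.036 | 0.045 | 0.021 | 0.024 | 0.015 |

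The six splits from 5:15 to 10:10 also stay below 5% when the 6-month risk is varied from 5% to 20%.

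**Exact version.** The permutation log-rank has a size of 0.003 (10:10) to 0.025 (3:17) over the same splits, so it never exceeds 5%. It cannot supply events. For a hazard ratio of 0.5, a 1:1 split and two-sided 5%, 80% power needs 4(1.96 + 0.842)²/(ln 0.5)² = 65.3, that is 66 deaths. With 2 to 3 deaths the power is about 7% to 9%.

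**The case against.** The strongest reply is that the document never says the test is asymptotic. It names a log-rank test, and how its p-value is computed may be settled in an analysis plan that is not shown. In section 2.6 the word exact also qualifies confidence intervals; no exact test is named for any endpoint. This stands as a limit: the chi-square version is the default reading of the text, not a statement in it.

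A second reply also stands. Survival is secondary and is to be summarised. The one-sided 0.05 belongs to the primary endpoint, and the only threshold with a consequence is 50% completion. No decision hangs on these p-values.

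A reader might infer three stronger things that the documents do not support.

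- *That false positives are generally inflated.* Averaged over deaths, the test is conservative at six of the nine splits examined. The highest conditional figure, 20%, needs exactly one death and a 4:16 split. The article gives no expected proportion of non-responders, so a very lopsided split is possible but not predicted.
- *That near-equal cohorts with one to three deaths can never give p < 0.05.* This holds at 10:10 but fails at 9:11 (0.042) and 8:12 (0.023).
- *That an exact test would rescue the comparison.* It removes the p-values that are too small, but it is even less able to detect a difference.

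**Conclusion.** The point holds in limited form and is minor. With about 2.4 expected deaths, the default log-rank p-value at 6 months is unreliable. For particular outcomes in unequal cohorts it can be several times too small (0.046 against 0.20; 0.024 against 0.079). On average, a nominal 5% test has a true size between 1.5% and 7.9% over splits from 2:18 to 10:10, and exceeds 5% only when the smaller cohort has 4 patients or fewer.

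This rests on four assumptions: the chi-square reading of the named test; a constant hazard from a survival figure quoted as a lower extreme, so that better survival means fewer deaths; no censoring before 6 months; and a split that the documents leave open. It applies to the 6-month analysis only. Survival is also collected later by record review, and the same hazard would give about 8 deaths by 24 months. Cancer-specific survival can have no more events than overall survival, so it is at least as sparse.

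**What to change.** In section 2.6, remove the log-rank p-values for overall and cancer-specific survival at 6 months. Report deaths over patients in each cohort with exact 95% confidence intervals beside the Kaplan-Meier plots. If a p-value is wanted, specify the exact (permutation) log-rank.

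The intervals show how little the data can say. With one death in 4 and none in 16, the log-rank p is 0.046. The exact interval for 1/4 runs from 1 − 0.975^(1/4) = 0.6% to 80.6% (the solution of (1 − p)⁴ + 4p(1 − p)³ = 0.025), and for 0/16 from 0% to 1 − 0.025^(1/16) = 20.6%.

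The change costs one phrase in section 2.6 or the analysis plan, and brings survival into line with the exact intervals already chosen for the other endpoints. The downside is that no significance test for survival at 6 months remains, but the expected number of deaths could not support one. If the analysis plan already specifies an exact version, adding that word to section 2.6 is enough to remove the too-small p-values.
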